#### 4.3. Sponsor's Responsibilities

##### 4.3.1. Study drug: pyronaridine and artesunate

Pyronaridine artesunate and its matching placebo will be manufactured by Shin Poong Pharm Co. Ltd in accordance with appropriate quality (GMP) standards. The manufacturer will supply certificates of analyses and a statement of the expiry or re-test dates. Drug supplies will be shipped to the Investigational site after all necessary ethical and local authority's approval have been provided.

Shin Poong will provide study drug packaged to prevent contamination or deterioration during transport and storage. Shin Poong have determined acceptable storage temperatures, conditions and times to be observed for study drug and will inform the study site of these. Expiry dates are provided on the labelled study material.

#### **4.3.2. Comparator drug: chloroquine**

Chloroquine and its matching placebo will be manufactured by Shin Poong Pharm Co. Ltd in accordance with appropriate quality (GMP) standards. Shin Poong Pharm Co. Ltd will supply certificates of analyses and a statement of the expiry or re-test dates. Drug supplies will be shipped to the Investigational site after all necessary ethical and local authority's approval have been provided.

Shin Poong will provide study drug packaged to prevent contamination or deterioration during transport and storage. Shin Poong have determined acceptable storage temperatures, conditions and times to be observed for study drug and will inform the study site of these. Expiry dates are provided on the labelled study material.

#### **4.3.3. Primaquine**

Primaquine will be manufactured by Shin Poong Pharm Co. Ltd in accordance with appropriate quality (GMP) standards. Shin Poong Pharm Co. Ltd will supply certificates of analyses and a statement of the expiry or re-test dates. Drug supplies will be shipped to the Investigational site after all necessary ethical and local authority's approval have been provided.

Shin Poong will provide study drug packaged to prevent contamination or deterioration during transport and storage. Shin Poong have determined acceptable storage temperatures, conditions and times to be observed for study drug and will inform the study site of these. Expiry dates are provided on the labelled study material.

#### **4.4. Storage Conditions**

Clinical trial material is to be stored under the strict conditions stipulated by Shin Poong Pharm.

Stability testing has been conducted prior to the conduct to this trial to confirm the stability of the clinical trial material.

#### **4.5. Drug Administration**

Study drug will be administered to patients by a qualified member of the study site who has been designated by the Investigator. All parties will be blind to treatment assignment and will not be informed of treatment allocation unless the blind needs

to be broken for a medical emergency. Sealed envelopes with treatment allocation will be available at each site to be opened only in case of emergencies. Patient's weight at screening should be used to calculate the number of tablets to be administered.

Study drug will be given to each patient with up to 240 ml (full glass) water. All tablets must be swallowed. Patients will take the medication in an upright position (seated or standing). The patient may be given food prior to drug administration. Initial drug administration day is designated Day 0. A dispensing record detailing the number of tablets administered for each patient, as well as the date and time, will be maintained. Exact time of dose administration will be recorded in the CRF. Dosing on the two subsequent days will occur no less than 10 hours after the previous dosing. Exact time of daily dose administration will be recorded in the CRF.

In the case of a patient vomiting the first dose (Day 0) within 0 to 30 minutes of study drug administration, a repeat full dose will be given. If patient vomits the study drug on either the second (Day 1) or third day (Day 2) of dosing or if the patient vomits a re-administered dose on Day 0, they will not be re-dosed and will be withdrawn from the study. A patient who is withdrawn due to vomiting must be given rescue medication.

Unused medication will remain in a locked cabinet in the pharmacy until full accountability has been performed by the Sponsor or its designee and instructions given for their return to Shin Poong.

Patients with normal G-6-PD activity (as at screening) and who complete the study up to Day 28 will be given a 14-day course of primaquine (15 mg/day) in an open-label manner starting on Day 28, after all required assessments have been completed. For women of childbearing potential, a negative pregnancy test should be demonstrated before starting primaquine treatment. Primaquine treatment should not be administered to pregnant women.

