| Number of Patients and Randomisation | A total of 456 patients from approximately 6 to 7 study sites will be randomised, with a maximum of 100 patients to be included per site. Patients will be randomly assigned in a 1:1 ratio to one of the following treatment arms:
pyronaridine artesunate (180:60 mg tablets) + chloroquine-placebo
or
chloroquine (155 mg tablets) + pyronaridine artesunate-placebo                                                                                                                                                                                                                                                                                                                                                                                                                                                                                                                              |
| Trial Design                         | The trial is designed as a multicentre, randomised, double-blind, double-dummy, comparative study of the efficacy and safety of a three day regimen of the fixed combination of pyronaridine artesunate (3:1) versus chloroquine.
Patients will be followed for safety for 42 days after the first study drug administration. The primary efficacy endpoint will be at Day 14.

Except for patients who are deficient in glucose-6-phosphate dehydrogenase (G-6-PD), patients completing the study up to Day 28 shall be given a 14-day course of primaquine (15 mg/day) starting on Day 28, after all required assessments have been completed (including demonstration of a negative pregnancy test for women of childbearing potential). Patients who are deficient in G-6-PD and who complete Day 28 will be treated as per country policy. All patients will have a final assessment on Day 42. |

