### 3. METHODS AND INVESTIGATIONAL PLAN

#### 3.1. Study Design Overview

The study is designed as a multicentre, randomized, double-blind, double-dummy, parallel group, comparative trial.

Patients will be randomized to receive either oral pyronaridine artesunate (180:60 mg tablets), plus chloroquine-placebo or oral chloroquine (155 mg tablets), plus pyronaridine artesunate-placebo, once a day for 3 consecutive days. Patients will be followed for 42 days after the first study drug administration, the primary efficacy endpoint occurring at Day 14.

For patients who complete the study up to Day 28 and who have normal G-6-PD-activity, a 14-day course of primaquine (15 mg/day) shall be administered starting on Day 28, after all required assessments have been performed, to complete their radical cure. Patients who are deficient in G-6-PD and who complete the study up to Day 28 will be treated as per country policy. For all patients, a final safety assessment will be performed on Day 42.

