##### 3.2.1. Inclusion criteria

Patients must fulfil the following inclusion criteria to be eligible for enrolment in the study:

1. Male or female patients between the age of 3 and 60 years, inclusive.
2. Body weight between 20 kg and 90 kg with no clinical evidence of severe malnutrition.
3. Presence of acute uncomplicated *P. vivax* mono-infection confirmed by:

- a. Fever, as defined by axillary/tympanic temperature  $\geq 37.5^{\circ}\text{C}$  or oral/rectal temperature  $\geq 38^{\circ}\text{C}$ , or history of fever in the previous 24 hours (history of fever must be documented) **and**,
  - b. Positive microscopy of *P. vivax* with parasite density  $\geq 250/\mu\text{L}$  of blood (including at least 50% of asexual parasites)
4. Written informed consent, in accordance with local practice, provided by patient and/or parent/guardian/spouse. If the patient is unable to write, witnessed consent is permitted according to local ethical considerations.
5. Ability to swallow oral medication.
6. Ability and willingness to participate based on information given to patient or parent or guardian and access to health facility.

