**4.2.3. Primaquine**

Primaquine will be supplied by Shin Poong Pharm Co. Ltd. Clinical trial material will be presented in an open-label manner, in high density polyethylene bottles.

The dosage to be used for adults is 15 mg primaquine on Days 28 through 42. The tablet strength to be used is 26.3 mg primaquine phosphate (equivalent to 15 mg primaquine base), which will provide a posology for adults of 1 tablet every day for 14 consecutive days, starting on Day 28 (see Attachment 4).

The dosage to be used for children is 0.5 mg/kg primaquine phosphate (equivalent to 0.3 mg/kg primaquine base) per day (see Attachment 4).

Note: Due to the risk of haemolytic anemia in G-6-PD-deficient patients, primaquine shall be administered only to patients with normal G-6-PD activity (as determined at baseline). Furthermore, for women of childbearing potential, primaquine will only be administered once a negative pregnancy test has been demonstrated.

Example Product Label for primaquine:

|                                                                                                                                                                                                                                                                                                                                                                                                                                       |
|---------------------------------------------------------------------------------------------------------------------------------------------------------------------------------------------------------------------------------------------------------------------------------------------------------------------------------------------------------------------------------------------------------------------------------------|
| 
Product for Clinical Study Use ONLY
 
Study Reference: SP-C-006-06
 
Patient number:
 
Study Visit: Day 28 through Day 42
 
Contains: 14 Tablets
 
Each tablet contains:
 
primaquine base 15 mg
 
Storage:
 
Lot No.:
 
Expiration date:
 
To be administered by Study Staff only
 
Sponsor: SHINPOONG PHARM. Co., Ltd., Republic of Korea
 |

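### The synopsis and sections 3.1 and 4.5 state primaquine 15 mg/day without limiting it to adults, which contradicts the half-tablet dose in Attachment 4 for children of 20-35 kg

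*Protocol*

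**What the plan says.** Three places in the protocol give a single primaquine dose for the radical-cure course:

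- Synopsis, Trial Design: "patients completing the study up to Day 28 shall be given a 14-day course of primaquine (15 mg/day) starting on Day 28". The exceptions concern G-6-PD deficiency and pregnancy.
- Section 3.1: "a 14-day course of primaquine (15 mg/day) shall be administered starting on Day 28". The condition is normal G-6-PD activity; pregnancy is not mentioned here.
- Section 4.5: "will be given a 14-day course of primaquine (15 mg/day) in an open-label manner starting on Day 28". The conditions again concern G-6-PD status and pregnancy.

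None of the three makes the dose depend on age or weight, and none refers to Attachment 4 for primaquine. Children are eligible under section 3.2.1: "Male or female patients between the age of 3 and 60 years, inclusive" and "Body weight between 20 kg and 90 kg".

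The sections that set the dose in detail say something different. Section 4.2.3 gives separate rules: "The dosage to be used for adults is 15 mg primaquine on Days 28 through 42", and "The dosage to be used for children is 0.5 mg/kg primaquine phosphate (equivalent to 0.3 mg/kg primaquine base) per day". It refers to Attachment 4 for both. The children's chart there gives half a 15 mg tablet at 20-35 kg and one tablet above 35 kg. Section 5.2.1.2 has patients weighed again on Day 28 so that the primaquine tablet count can be read from that chart.

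**The concern.** For a G-6-PD-normal child of 20-35 kg, 15 mg/day and 7.5 mg/day cannot both be the dose. The contradiction matters most in section 4.5, because that is the drug-administration section and its primaquine paragraph states a fixed dose without sending the reader to the chart.

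Two other features make the flat dose easier to take as intended. The synopsis separates adult and child doses for chloroquine but not for primaquine. The only example primaquine label shows 14 tablets of 15 mg, which one tablet a day uses up exactly in 14 days, whereas a child on half a tablet needs 14 × 0.5 = 7. Neither would alert a site to a misreading.

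What is at stake is the dose given to the lightest children and the consistency of the late data. If some sites followed section 4.5 and others followed Attachment 4, adverse events from Day 28 to Day 42, Day 42 haematology and the exploratory Day 42 cure rate could differ between sites in this weight group for a reason unrelated to the randomised drugs.

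**Working it through.** **Inputs**

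- Flat dose: 15 mg base per day for 14 days (synopsis; sections 3.1 and 4.5).
- Child rate: 0.3 mg/kg base per day (section 4.2.3).
- Tablet strength: 15 mg base (section 4.2.3, Attachment 4).
- Children's chart: 0.5 tablet at 20-35 kg, 1 tablet above 35 kg (Attachment 4).

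**Step 1: reproduce the chart row.** Target dose = 0.3 × weight; tablets = target / 15.

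| Weight | Target (mg) | Tablets | Nearest half tablet |
|---|---|---|---|
| 20 kg | 0.3 × 20 = 6.0 | 0.40 | 0.5 |
| 25 kg | 0.3 × 25 = 7.5 | 0.50 | 0.5 |
| 35 kg | 0.3 × 35 = 10.5 | 0.70 | 0.5 |

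The half-tablet row for 20-35 kg therefore follows from the rate in section 4.2.3. The chart dose is 0.5 × 15 = 7.5 mg/day, and no calculation in the protocol is wrong.

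**Step 2: compare the flat dose with the chart.**

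| Weight | Flat dose | Chart dose | Ratio |
|---|---|---|---|
| 20 kg | 15/20 = 0.75 mg/kg | 7.5/20 = 0.375 mg/kg | 2.0 |
| 25 kg | 15/25 = 0.60 mg/kg | 7.5/25 = 0.30 mg/kg | 2.0 |
| 35 kg | 15/35 = 0.43 mg/kg | 7.5/35 = 0.21 mg/kg | 2.0 |
| 36 kg | 15/36 = 0.417 mg/kg | 15/36 = 0.417 mg/kg | 1.0 |

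The ratio is 15/7.5 = 2 across the whole 20-35 kg row. Over 14 days it is 14 × 15 = 210 mg against 14 × 7.5 = 105 mg. Above 35 kg the chart itself gives one tablet, so there is no conflict.

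**Step 3: compare the flat dose with the 0.3 mg/kg rate.** 15/6.0 = 2.5 at 20 kg, 15/7.5 = 2.0 at 25 kg and 15/10.5 = 1.43 at 35 kg. The excess over the intended rate is largest in the lightest children.

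**Step 4: see which endpoints come after primaquine.** Primaquine starts only once the Day 28 assessments are done. Cure on Days 14, 21 and 28, parasite and fever clearance times, and clearance on Days 1 to 3 are all settled by then. Only the Day 28-42 safety data and the exploratory Day 42 endpoints follow.

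**The case against.** The strongest reply is that the protocol already gives the right rule wherever it sets the dose in detail. Section 4.2.3 separates adults from children, section 5.2.1.2 orders a Day 28 weighing for this purpose, and Attachment 4 holds the chart. The synopsis and section 3.1 are overviews. The Day 28 entry in section 6 lists weight and then primaquine once daily for 14 days with no milligram figure, and the Study Plan footnote gives none either. A site would have to overlook all of this to double the dose. That stands, and it limits the practical weight of the point. It does not remove the contradiction, because section 4.5 is itself an operative section and states a dose that is wrong for these children. The monitors' drug counts under section 4.7 could reveal a misreading, but possibly only after the doses had been taken.

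Three stronger readings are tempting, and the protocol does not support them.

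- *Section 4.5 bases primaquine on the wrong weight.* It does say that the patient's "weight at screening should be used to calculate the number of tablets to be administered", but this stands in the opening paragraph on the blinded study drug. Section 5.2.1.2 assigns the screening weight to study drug and the Day 28 weight to primaquine, so there is no conflict.
- *Days 28 through 42 implies a fifteenth dose.* The span covers 15 calendar days, but section 4.2.3 itself specifies 14 consecutive days and the label shows 14 tablets. A course begun on Day 28 or Day 29, within the visit window, ends on Day 41 or Day 42 and lies inside the span.
- *The paediatric dose is missing.* It is present; only the adult qualifier is absent in three places.

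**Conclusion.** The point holds as an internal inconsistency, minor to should-fix. Its size is exactly a factor of 2 for children of 20-35 kg and nil above 35 kg. It is conditional on a site following section 4.5 literally instead of section 4.2.3, section 5.2.1.2 and Attachment 4. The protocol does not say how many children in this weight range are expected, so no number of affected patients can be given.

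A reader might infer that the efficacy conclusions are at risk. They are not. The Day 14 primary endpoint and the secondary efficacy endpoints precede primaquine, and the same primaquine rule applies in both arms, so the between-arm comparison is not affected. The sample size and the non-inferiority test are untouched. The case for acting is that a contradictory paediatric dose in the administration section can be removed at almost no cost.

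**What to change.** In the synopsis (Trial Design), section 3.1 and section 4.5, replace the bracketed daily dose with: *adults 15 mg/day; children by Day 28 weight per Attachment 4*. This brings the three places into line with sections 4.2.3 and 5.2.1.2. Attachment 4, the label, the schedule and the Study Plan can stay as they are.

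The cost is a few words in a short protocol amendment. It needs no additional patients, visits, samples or relabelling, and no change to the analysis.

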#### **4.6. Emergency Unblinding**

Sealed envelopes containing the study medication assignment for each patient will be provided to the Investigator. The envelopes will be retained by the Investigator (or designee) in a secure area and may be may be opened in case of emergency only if the Investigator(s) need to know the study medication in order to manage the patient's condition. The Sponsor must be notified before breaking the blind, unless identification of the study medication is required for emergency

therapeutic measures. The Sponsor must then be notified within 24 hours of the blind being broken. The date that the blind was broken, the reason for the unblinding and the name of the person performing the unblinding must be recorded in the source documents and on the CRF. All code break envelopes (opened and unopened) will be returned to the Sponsor at the end of the study.

#### **4.7. Compliance**

Every attempt will be made to select patients and carers who have the ability to understand and comply with instructions, in particular the requirements for patients to attend the scheduled study visits.

The staff member designated by the Investigator to administer the study drug will ensure that each patient receives and swallows the appropriate number of tablets by direct observation and monitoring of drug administration. Monitors will perform drug counts and compliance for each patient on an ongoing basis during monitoring visits. Drug accountability records will be maintained by the designated clinical study site personnel on specific documentation forms provided by the Sponsor.

#### **4.8. Study Site's Responsibilities**

Upon receipt of study drug, the Principal Investigator will conduct an inventory and sign the accompanying receipt and return this to the Sponsor.

Study drugs packs will be stored under the control of the Principal Investigator in a locked cabinet in a secure facility appropriate for the advised storage conditions and nature of products.

Clinical trial material may be used only in the conduct of this study and any unused medication must be returned as instructed by Shin Poong on completion of the study.

#### **4.9. Clinical Study Material Accountability**

A drug accountability utilisation log will be maintained for clinical study material. This will include the date and time of administration, quantity administered, lot number and patient randomisation number. The log should be signed and dated by the dispenser.

At the end of the study, accountability will be checked by the Sponsor or designee, and the Sponsor and the Principal Investigator will retain copies of the complete logs.

Unused supplies will be returned in accordance with written instructions from Shin Poong.

#### **4.10. Concomitant and Forbidden Medication**

Patients should not have taken any other antimalarial therapy in the 2 weeks preceding the first study drug administration, as evidenced by the Saker Solomon and Lignin tests.

Treatment of fever over 38.0°C (axillary/tympanic) or 38.5°C (oral/rectal) with paracetamol (acetaminophen) up to 1000 mg, according to age of patient, is permitted. Concomitant disease and/or adverse events requiring treatment may be treated according to local practice.

Antimalarials and antibiotics with antimalarial activity including macrolides and cyclins are not allowed during the study except tetracycline for ophthalmic use. A list of forbidden medication is provided in Attachment 5.

Name (generic), dosage (only for antipyretics), dates of administration and reason for administration of any medication given during the study must be recorded in the CRF. If the medication is given to treat an adverse event, the appropriate adverse event form must be completed.

#### **4.11. Rescue Medication**

Treatment failures will be treated with the best antimalarial therapy available in the country where the study is conducted. All procedures to be performed at Day 28, including sampling for PCR, preparation of a thin and thick films and **whole blood sample for measurement of pyronaridine and/or chloroquine/chloroquine metabolites blood levels** must be undertaken before rescue medication is administered.

## 5. ASSESSMENTS

### 5.1. Efficacy Assessments

#### 5.1.1. Parasitological assessments

##### 5.1.1.1. Microscopy

Parasite density expressed as the number of parasites per microlitre ( $\mu\text{L}$ ) of blood will be measured serially to determine parasite clearance time (PCT). Asexual parasite and gametocyte counts will be recorded separately at screening, while total parasite counts will be recorded at any timepoint thereafter. Blood sampling for parasitology will be done usually by means of finger prick except when the timing for parasitology assessments coincide with time for clinical laboratory tests, in which cases, blood smears (thick and thin) and blood drop for PCR can be taken from the venous blood collected for clinical laboratory analyses.

Blood smears preparation, staining, examination and interpretation should be in accordance with the guidelines provided by the Sponsor. Any deviation from the Sponsor guidelines must be discussed and approved by the Sponsors before the study commences.

Thick and thin blood films for parasite count should be obtained and examined at screening on Day 0 to confirm inclusion/exclusion criteria. Thick blood films will be examined every 8 hours (+/- 1 hour) following first dose administration and for at least 72 hours (Day 1 and Day 2) or until the parasites have cleared as evidenced by two consecutive negative slide readings taken 8 to 24 hours apart. To avoid disruption of patient sleep at night, the first interval between the first dose administration and the next smear may be shorter or longer than 8 hours but shall not exceed 12 hours.

Thick blood films will be also examined on Days 3, 7, 14, 21, 28, 35 and 42 or on any other day if the patient spontaneously returns. Additionally, blood films should be obtained whenever parasitological reassessment is required. A thin blood smear will also be taken from Day 7 whenever parasitological blood samples are taken, and reserved in the event of recrudescence, to confirm *Plasmodium* species.

